### Study design and randomization

This type 3 hybrid implementation-effectiveness study will test two discrete implementation strategies for improving professional interpreter use (primary implementation outcome) and patient comprehension (secondary effectiveness outcome) in primary care. The implementation strategies—interactive web-based educational modules and access to mobile video interpreting—target different sets of barriers to professional interpreter use, an evidence-based practice [20, 21, 34, 82, 83]. Our results will therefore provide insights into how best to promote implementation of a well-studied, well-established practice known to improve outcomes but inconsistently used. As the potency of barriers may vary by provider and clinic, we will test the strategies alone and in combination, using a SMART design, with provider-level randomization.

A total of 55 providers from 3 to 5 primary care clinical organizations will be randomized 1:1 to either education or mobile video interpreting access, stratified by baseline interpreter use and clinic (phase 1; Fig. 2). Randomization will occur within REDCap, using a sequence generated by the study biostatistician and implemented by a research coordinator. After 9 months, providers with interpreter use in the top tertile (within strategy) will remain with the original strategy; those in the bottom two tertiles will be randomized 1:1 again, to continue the original strategy or to add the second strategy to the first (phase 2). After another 9 months of data collection, we will provide free access to both mobile video interpreting and educational modules to all enrolled providers and then track voluntary uptake by those not previously exposed for another 9 months (phase 3). Data collection will include *administrative data* to track interpreter use (primary outcome); *patient surveys and qualitative interviews* to determine diagnosis comprehension (secondary outcome) and communication quality; *provider surveys and qualitative interviews* to assess contextual and intrapersonal barriers and moderators; and *visit video recording* to capture additional barriers and determine fidelity of strategy implementation. We will assess each strategy’s effectiveness, alone and in combination, for improving professional interpreter use and patient comprehension. We will explore mechanisms by which these strategies work and evaluate the relative strategy-specific costs.

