#### Interpreter use

Interpreter vendor invoices will be collected from companies that clinics currently contract with; mobile video interpreting invoices will be managed by the study team. All professional interpreter invoices (not just mobile video interpreting) will be matched to clinic visits for patients who use a language other than English (all languages) for enrolled providers. We will calculate baseline interpreter use for enrolled providers for the six months pre-randomization and then randomize 1:1 to education or mobile video interpreting, stratified by baseline use and clinic. We will calculate interpreter use, both overall and strategy consistent, continuously throughout phases 1–3; other data collection will end after phase 2.

For analysis, interpreter use will be defined as a dichotomous variable at the level of the clinic visit. Visits with patients who use a language other than English with any billed professional interpreter use will be coded as “yes,” and the remainder will be coded as “no.”

Sample size calculations consider aim 1 group comparisons (mobile video interpreting, education, combination) at the end of phase 2. We assume loss of up to 9 providers (e.g., to job change; 16%) over the study; we expect attrition (up to 27%) in provider interviews and surveys, but that will not impact aim 1 power. With 5796 total encounters with patients who use a language other than English (7 visits/provider/month), we expect 1932 non-English visits per group, which will provide > 80% power to detect a 5% difference in proportion of professionally interpreted visits by groups [46, 57]. This will be readily feasible with administrative data.

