#### Patient/parent comprehension

Patient comprehension will be determined by asking surveyed patients (*n* = 648) to report the diagnosis they received during their visit with an enrolled provider. The parent-reported diagnosis will then be compared to the provider-documented diagnosis, which trained abstractors will have abstracted from the EMR. Two coders blinded to study assignment will compare the documented diagnosis to the patient-reported diagnosis to determine comprehension, coded as yes, concordant; no, not concordant; or unclear, based on the standard of whether a different follow-up provider would likely know the diagnosis based on the information provided by the patient. For analysis, comprehension will be coded as yes or no/unclear. We have successfully used these procedures previously [46].

In addition to measuring comprehension, the survey will use validated measures to collect demographics and satisfaction with communication and interpretation. The tablet-based survey will have an audio feature to allow patients to read or hear the questions in 4 non-English languages. The survey will be completed in the clinic whenever possible; otherwise, the patient will complete it within 7 days, independently online or over the telephone with a bilingual research coordinator or professional interpreter.

Based on aim 1 analyses, with 216 completed patient surveys per group (648 total), we will have ≥ *80% power to detect a 14% difference in diagnosis comprehension by group* [46]. This will also be feasible, achieved by surveying 7–12 patients per clinic per month for 18 months.

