#### Aim 1: Compare the effectiveness of two implementation strategies, alone and in combination, to improve use of interpretation and comprehension for patients/parents with language barriers seen in adult/pediatric primary care settings

We hypothesize that, compared to educational modules, provider access to mobile video interpreting will lead to (*H1*) greater odds of interpreter use for visits with patients/parents with language barriers (primary outcome) and (*H2*) better comprehension among patients/parents with language barriers. We also hypothesize (*H3*) that mobile video interpreting and educational modules together will yield greater odds of interpreter use than either strategy alone.

To test *H1* and *H3*, we will use assigned strategy and data collected during phases 1 and 2. Under the SMART design, comparisons of first-stage interventions, comparisons of second-stage interventions, and comparisons of the adaptive intervention with both stages can be conducted simultaneously using standard software with a technique called a “weighted and replicated” regression approach, using weighted generalized estimating equations (GEE) [66, 97]. Weighted GEE allows us to work with binary outcomes and weights and adjust for clustering within providers. Within-clinic correlations will be assessed by including clinic-specific random effects in our regression models and estimating the intra-cluster correlation coefficients. Significance of the intra-cluster correlation coefficients will be examined by comparing models with and without clinic-specific random effects using likelihood ratio tests. If no strong within-clinic correlation is detected, we will use fixed-effects regression models for their better power; otherwise, estimates and inference based on random-effects regression models will be reported. *H1* and *H3* will be tested using the Wald test and robust standard error estimates [66, 97]. Model-based estimates of odds ratio comparing education to mobile video interpreting or both will be reported, along with 95% confidence intervals [98].

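### The stated power for interpreter use counts visits as if independent although providers are randomized, so it holds only at a very small within-provider correlation; the comprehension figure has the same gap but is merely fragile

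*Protocol article*

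**What the plan says.** Under Study design and randomization, the unit of randomization is the provider: the trial proceeds "using a SMART design, with provider-level randomization", and "A total of 55 providers from 3 to 5 primary care clinical organizations will be randomized 1:1".

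The power text for the primary outcome is in the section Interpreter use. It sets the comparison ("Sample size calculations consider aim 1 group comparisons (mobile video interpreting, education, combination) at the end of phase 2") and allows for attrition ("We assume loss of up to 9 providers (e.g., to job change; 16%) over the study"). It then counts visits: "With 5796 total encounters with patients who use a language other than English (7 visits/provider/month), we expect 1932 non-English visits per group". From that count it claims more than "80% power to detect a 5% difference in proportion of professionally interpreted visits by groups".

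The section Patient/parent comprehension does the same with 216 surveys per group (648 in all), claiming at least "80% power to detect a 14% difference in diagnosis comprehension by group".

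Neither section gives an ICC, a design effect, a number of providers per group or a base rate. The Aim 1 analysis section does recognise the clustering: "Weighted GEE allows us to work with binary outcomes and weights and adjust for clustering within providers".

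**The concern.** Visits to the same provider tend to be alike in whether an interpreter is used. When providers are randomized, that likeness inflates the variance of the group comparison by 1 + (m − 1) × ICC, where m is the number of visits per provider. With m above 100, even a small ICC matters, and the number of providers, not of visits, limits precision.

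A power figure computed on independent visits therefore belongs to a different analysis from the clustered one planned. H1 and H3 concern the primary outcome and are meant to help organizations choose a strategy. A reader who trusts the stated power would treat a non-significant result as stronger evidence against a 5-point difference than the trial can supply.

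**Working it through.** **Inputs from the article.** 55 providers less 9 losses = 46. Visits: 7 per provider per month over 18 months (phases 1 and 2) = 126 per provider. Three groups. Surveys: 648, or 216 per group.

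**Assumptions.** Two-sided 5% test (the article plans 95% intervals); equal visits per provider; ICC from 0.01 to 0.10; base rate (the lower of the two proportions) of 17–80% for interpreter use and 43–75% for comprehension. The Background gives 17–45% for interpreter use in acute care; the power text gives no base rate.

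**Step 1: the plan's own figures.** 46 × 7 × 18 = 5796, and 5796 / 3 = 1932, as stated. The number per group for 80% power with independent observations is

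n = [1.96·√(2p̄(1−p̄)) + 0.8416·√(p₁(1−p₁) + p₂(1−p₂))]² / (p₂−p₁)².

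- Interpreter use, least favourable case, 47.5% v 52.5%: n = (1.386 + 0.594)² / 0.0025 ≈ 1569. With 1932 independent visits, power is 87.5%, and higher at other base rates. The claim of more than 80% reproduces.
- Comprehension, least favourable case, 43% v 57%: n = 200. With 216 independent surveys, power is 83%. The claim of at least 80% reproduces.

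**Step 2: largest ICC that keeps 80% power for 5 points.** Maximum ICC = (1932/n − 1) / 125.

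- 47.5%: (1932/1569 − 1)/125 = 0.0019
- 17%: (1932/985 − 1)/125 = 0.0077
- 80%: (1932/906 − 1)/125 = 0.0091

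At use near 50%, an ICC of 0.002 means that providers' true rates have a standard deviation of √(0.002 × 0.25) = 0.022, about 2 percentage points.

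**Step 3: power for 5 points with clustering.** Effective n = n / (1 + 125 × ICC). For H1, 46 providers split 23 v 23 give 23 × 126 = 2898 visits per arm.

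| ICC | Design effect | Effective n from 1932 | Power, 1932 per group | Effective n from 2898 | Power, 23 v 23 providers |
|---|---|---|---|---|---|
| 0.01 | 2.25 | 859 | 54–78% | 1288 | 72–92% |
| 0.02 | 3.50 | 552 | 38–59% | 828 | 53–76% |
| 0.05 | 7.25 | 266 | 21–33% | 400 | 29–46% |
| 0.10 | 13.5 | 143 | 13–20% | 215 | 18–28% |

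Ranges run over base rates of 17–80%; the low end is near 50%.

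More visits do not cure this. With unlimited visits, effective n tends to (number of providers)/ICC. At ICC 0.05 that is 15.3/0.05 = 307 per group, and power for 5 points is at most about 24–37%.

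**Step 4: comprehension, 14 points.** m = 648/46 = 14.1; the design effect is 1.13 at ICC 0.01, 1.65 at 0.05 and 2.31 at 0.10.

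| ICC | 216 per group | 324 per arm (H2, two arms) |
|---|---|---|
| 0.01 | 78–95% | 92–99% |
| 0.05 | 62–84% | 79–95% |
| 0.10 | 48–71% | 65–87% |

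Ranges run over base rates of 43–75%.

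**The case against.** **The article never says that visits were taken as independent.** True. It is inferred from the missing ICC and from the match with the independent formulas. But the article prints the count, the effect and the power together, and for 1932 visits per group they agree only at an ICC below 0.01 for base rates of 17–80%. An ICC in a fuller document could not make them agree at a larger value.

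**H1 is a two-arm contrast, and baseline use could be adjusted for.** Both help. At ICC 0.01, 23 v 23 providers reach 80% at base rates such as 17%, 20%, 70% and 80%, though not near 50%. Suppose adjustment uses six baseline months (42 visits) and true provider rates correlate c = 0.8–0.9 between periods. Then r² = c² × [42ρ/(1+41ρ)] × [126ρ/(1+125ρ)], with ρ the ICC, which is 0.38–0.49 at ρ = 0.05. Effective n for 23 v 23 rises from 400 to about 648–776, and power to about 44–74%. That is a real gain, still short of 80%, and the stated calculation does not mention it.

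**Stratification and tertiles do not prove large provider differences.** Also fair: a tertile split is a ranking and can be made at any spread. These features show that the plan expects some variation, not how much.

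**The analysis itself is clustered.** This stands. Robust standard errors and 95% intervals would show the imprecision, so the planned inference is not invalid. The fault lies in the planning figure.

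**Stronger readings that a reader might infer.** One is that neither power figure survives any ordinary ICC. The comprehension results in the second table do not support that. Another is that the trial cannot see differences below some fixed size. Any such figure depends on an assumed ICC and base rate, and the article gives neither. A third is that the parallel-group design effect also describes H3. It does not: the combination starts only in phase 2, in providers who already had one strategy, so H3 is partly a within-provider comparison, with about 63 combination visits per provider instead of 126.

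**Conclusion.** The point holds for the primary outcome and should be corrected. The power stated for 5 points is the independent-visit figure, and the design with 1932 visits per group delivers it only if the provider ICC is at most about 0.002 to 0.009, depending on the base rate. The more favourable two-arm H1 contrast can reach 80% at an ICC of about 0.01 away from a 50% base rate, but not at 0.05 for base rates of 17–80%.

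For comprehension the claim omits clustering too, but it is sensitive, not wrong throughout. With 216 per group it is close to or above 80% at ICC 0.01 and falls below 80% at ICC 0.05 unless the base rate is above roughly 70%. The H2 contrast with 324 per arm keeps about 80% or more at ICC 0.05. Withdrawing the 14% claim outright is not warranted.

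The visit counts are correct; what is wrong is the step from visits to power. The sizes rest on the assumptions listed above, since the article states no ICC, base rate or test level.

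**What to change.** - Estimate the provider ICC and the base rate of interpreter use from the six-month pre-randomization data that the article already plans to collect.
- Replace the 5% power statement with power or detectable differences for H1, computed from the number of providers, visits per provider and a range of ICCs (for example 0.01–0.20). If adjustment for baseline use is counted on, state the between-period correlation assumed.
- Compute H3 with a method that reflects re-randomization and the partly within-provider comparison, such as simulation of the weighted analysis, instead of the parallel-group design effect.
- Keep the 14% comprehension statement, but attach the ICC, base rate and contrast (two arms or three groups) on which it depends.

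Cost: rewording of the sample-size text and a modest calculation. No extra providers, visits or data are needed, and the planned analysis is unchanged. The downside is that the stated figures become less favourable.

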#### Patient/parent comprehension

Patient comprehension will be determined by asking surveyed patients (*n* = 648) to report the diagnosis they received during their visit with an enrolled provider. The parent-reported diagnosis will then be compared to the provider-documented diagnosis, which trained abstractors will have abstracted from the EMR. Two coders blinded to study assignment will compare the documented diagnosis to the patient-reported diagnosis to determine comprehension, coded as yes, concordant; no, not concordant; or unclear, based on the standard of whether a different follow-up provider would likely know the diagnosis based on the information provided by the patient. For analysis, comprehension will be coded as yes or no/unclear. We have successfully used these procedures previously [46].

In addition to measuring comprehension, the survey will use validated measures to collect demographics and satisfaction with communication and interpretation. The tablet-based survey will have an audio feature to allow patients to read or hear the questions in 4 non-English languages. The survey will be completed in the clinic whenever possible; otherwise, the patient will complete it within 7 days, independently online or over the telephone with a bilingual research coordinator or professional interpreter.

Based on aim 1 analyses, with 216 completed patient surveys per group (648 total), we will have ≥ *80% power to detect a 14% difference in diagnosis comprehension by group* [46]. This will also be feasible, achieved by surveying 7–12 patients per clinic per month for 18 months.

#### Provider attributes and organizational context

These data will be collected via 2 surveys and 3 interviews over the course of the study. Providers will complete a web-based survey at baseline, before initial randomization, to assess demographics and barriers to interpreter use via the TDF Questionnaire, [74] Organizational Readiness for Implementing Change (ORIC) questionnaire [80], and the Implementation Leadership Scale (ILS) [81]. We will repeat the survey at the end of phase 2, to capture changes over time and provider time and costs associated with the implementation strategies.

Enrolled providers will also complete qualitative interviews (1) before initial randomization, (2) during phase 1, and (3) during phase 2. Interviews will explore contextual and personal factors that serve as barriers, moderators, mechanisms, and proximal outcomes of interpreter use (see Figs. 3 & 4 for preliminary causal pathway diagrams). We will use qualitative interviews given the lack of survey measures for many factors, and concern for social desirability bias, as providers may not endorse interpreter nonuse on surveys but may be more likely to in the context of a conversation. Provider qualitative and quantitative data will be analyzed together (see “Data analysis”).

**Fig. 3 Fig3:**
[figure not shown]
Preliminary causal pathway diagram for mechanisms associated with education as a strategy

**Fig. 4 Fig4:**
[figure not shown]
Preliminary causal pathway diagram for mechanisms associated with mobile video interpreting as a strategy

#### Patient communication experiences

A subset of patients completing the survey will be invited to complete a 30-min qualitative interview [88]. Survey respondents who endorse having a concern about how their provider communicated with them will be invited to interview [89], as will a random sample of others (total *n* = 75). Our goal is to understand how communication occurred during the visit, how effective the patient found that communication to be and why, and the details of any concerns the patient had. The interview will be completed in the clinic prior to departure whenever possible; otherwise, the patient will have 7 days to complete it, over the telephone with a bilingual research coordinator or via professional interpreter, in one of our 4 eligible non-English languages.

We estimated initial qualitative sample size based on the heterogeneity of our target group, the number of research sites, and the complexity of the areas of inquiry. The initial sample estimates will be adjusted as needed to achieve data sufficiency [90].

#### Video recording

Video-recorded visits with patients who use a language other than English (*n* = 100) will provide granular, objective data regarding interpreter use, technical difficulties, communication delays, and provider use of best-practice techniques for communicating with an interpreter, to supplement provider- and patient-reported data. Trained coders will code videos for specific behaviors, based on the coding scheme developed previously [36], to provide data on barriers, mechanisms, proximal outcomes of interpreter use, and strategy fidelity (Table 1). The video recording sample size is based on our previous work and logistical considerations, with 100 recordings both feasible and likely to achieve data sufficiency.

#### Cost data

Administrative cost data collected from clinics will include costs associated with interpreter vendor invoices and contracts; interpreter-specific clinic hardware (e.g., dedicated speakerphones); wireless Internet; and educational module development, following recommendations for economic analysis in implementation science [91]. Provider-incurred time and costs will be collected via the final survey, including time spent on each strategy, excess data charges associated with mobile video interpreting use (if any), and wear or damage to personal devices. Study team time related to implementing each strategy (e.g., installing mobile video interpreting, reminder emails) will be tracked in real time, as they would be performed by clinic staff with real-world implementation. We do not expect changes in clinic visit length, based on time-motion studies of interpreted patient visits [92, 93].

### Data analysis

Primary quantitative analyses will be conducted using an intention-to-treat approach. Provider and patient characteristics will be summarized overall and by strategy. Missing data will be minimized through communication with participants regarding the importance of completing surveys and interviews, participant incentives, offering multiple languages and modalities for survey and interview completion, and completing surveys and interviews on-site when possible. For our primary outcome, we expect interpreter invoice data to be complete, given our previous experience [12, 46, 57]. We will track interpreter use for all enrolled providers for the entire study, even if they do not complete interviews or surveys. For our secondary outcome, diagnosis comprehension, patterns of data missingness will be examined. We expect randomization will help protect against imbalance in unobserved confounders, so our main concern will be with missing data. We will conduct sensitivity analyses based on multiple imputations to assess the impact of missing data, in which we will generate multiple imputed datasets with missing values imputed by pooling information from observed data, and then combine statistical inferences across the multiply-imputed datasets [94–96].

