#### Mobile video interpreting access

The mobile video interpreting access strategy will provide access to mobile video interpreting, technical support, a tip sheet for mobile video interpreting use, and an extra charger, shock-resistant case, disposable antimicrobial sleeves, and a positioning stand to support clinical use of the provider’s own device, along with quarterly reports on the enrolled provider’s interpreter use. Mobile video interpreting-assigned providers can use a study-issued smartphone instead of their own. The mobile video interpreting strategy aims to improve provider motivation, capability, and opportunity related to interpreter use, by decreasing cognitive overload, enhancing interpreter access skills, shifting provider beliefs about capabilities and the consequences of interpreter use, reinforcing use via satisfaction, and altering the environmental context and resources to make access easier and use more rewarding (Table 2).

*Access to mobile video interpreting* is achieved by downloading the application (app) online and then entering an access code linked to a billing account; after being entered, the code is no longer visible. Access can thus be controlled by study staff. Study staff will download and orient providers to the app, demonstrate use, and answer questions. *Technical support* will be offered on demand. A *tip sheet* will be emailed that includes mobile video interpreting instructions and best practices.

Several interpretation vendors have similar apps that can be downloaded onto personal devices but are rarely used in this way. These apps are HIPAA compliant, use end-to-end encryption, and are accessed with one touch (i.e., no additional log in or passwords); no data is downloaded to the device.

*Feedback to enrolled providers* will be provided quarterly with both strategies, as a report of the percent of visits with patients who use a language other than English for which the provider used professional interpretation.

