#### Patients

We will enroll 3 populations of adult patients or parents of pediatric patients (henceforth “patients”) who use a language other than English, all being seen by enrolled providers. For our *administrative population*, we will include administrative data from all patients who were recorded as using a language other than English in the medical record and were seen by enrolled providers, for the interpreter use outcome. For our *survey population*, we will enroll patients who prefer medical care in the four most common non-English languages across clinics, who are in clinic for an acute concern (e.g., sore throat, new ankle pain). These individuals will be invited to complete a survey (*n* = 648), and a subset will be invited to complete a 20–30 min qualitative interview (*n* = 75). We will also recruit patients for our *video-recording population* (*n* = 100). Patients who use a language other than English with any visit type who consent will be eligible for video recording.

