To test *H2*, our analytic sample will include only patients who completed a post-visit survey (*n* = 648). A weighted GEE logistic regression model predicting patient/parent comprehension at the visit level will be estimated. Baseline covariates will include the clinic, patient demographics (age, sex, language), and patient comorbid conditions [99–102], pooled at the provider level. Model-based estimates of the odds ratio comparing education to mobile video interpreting or both will be reported, along with 95% confidence intervals computed via parametric bootstrapping [98].

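### For comprehension (H2), randomising providers does not protect against differences by strategy in which patients are surveyed, and the planned multiple imputation does not cover eligible visits that were never surveyed

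*Protocol article*

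**What the plan says.** Study design and randomization describes a trial "using a SMART design, with provider-level randomization". The strategies are not concealed: under Mobile video interpreting access, "Study staff will download and orient providers to the app, demonstrate use, and answer questions".

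The survey population (Patients section) is made up of people attending an enrolled provider with an acute concern who prefer care in one of the four commonest non-English languages. "These individuals will be invited to complete a survey". Under Patient/parent comprehension, the 648 surveys are to be "achieved by surveying 7–12 patients per clinic per month for 18 months". They are done in clinic where possible, otherwise within 7 days online or by telephone. Blinding is stated for the two coders who judge concordance of diagnoses.

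For H2, the Aim 1 analysis section says "our analytic sample will include only patients who completed a post-visit survey". The covariates are clinic, age, sex, language and comorbid conditions, with pooling at provider level. The Data analysis section gives the reasoning on bias: "We expect randomization will help protect against imbalance in unobserved confounders, so our main concern will be with missing data". It then plans to examine patterns of missingness and to run sensitivity analyses by multiple imputation.

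**The concern.** The sentence moves from randomisation to missing data as the main remaining worry. That is sound for interpreter use, which takes every eligible visit from administrative data. For comprehension there is a further step between randomisation and analysis: which of the eligible visits yield a completed survey. This step comes after allocation, and the strategy has already acted during the visit before the survey is completed. A patient who understood little may be less inclined to complete a survey, and understanding is what the strategies are meant to change. Completion could therefore differ by strategy even if every recruiter were masked.

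If it does, the H2 odds ratio mixes the strategy effect with a difference in who answered, and its confidence interval gives no sign of this. The same comprehension difference is the denominator of the H4b cost-effectiveness ratio, so the bias would carry over to that result.

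**Working it through.** **1. The sequence of events for H2, from the article.**
- Providers are randomised and start an open strategy (Study design and randomization; Mobile video interpreting access).
- Patients are invited, and surveys are collected over 18 months, which is phases 1 and 2 (Patients; Patient/parent comprehension).
- Only completers are analysed (Aim 1, H2).

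Selection into the analysis set therefore follows allocation. For the primary outcome there is no such step: all visits by patients recorded as using another language are included, under a consent waiver (Patients; Regulatory approvals).

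**2. What each planned safeguard reaches.**

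| Safeguard | Reaches selection into the survey? |
|---|---|
| Blinded diagnosis coders | No; protects outcome assessment |
| Multiple imputation | Not as described; H2 is confined to completers, so unsurveyed eligible visits are outside it |
| Acute visits and four languages only | Partly; narrows the mix |
| Clinic, age, sex, language, comorbidity | Partly; measured factors only, and provider-level pooling limits adjustment for which of a provider's patients responded |
| Characteristics summarised by strategy | May reveal imbalance; does not correct it |

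Table 1 also collects health literacy, education and English proficiency from respondents. These are plausible drivers of both response and comprehension, but they are not on the H2 covariate list.

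**3. The plan's own figures.**
- Surveys: 648 / 18 = 36 per month; 36 / 5 = 7.2 and 36 / 3 = 12, which matches the stated 7 to 12 per clinic.
- Power: 216 per group, 14-point difference, two-sided 5% (alpha and base rate are assumed, as neither is stated). Over base rates from 30% to 80%, power runs from 83.1% (43% vs 57%) to 99.2% (80% vs 94%). The stated 80% or more reproduces when clustering is ignored.

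**4. Illustrative size of the bias.** All inputs here are assumptions. Suppose there is no true effect and two types of patient.

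Bias = (comprehension gap between types) × (difference in their mix between strategies).
- Smallest: 0.15 × 0.10 = 1.5 points; 1.5 / 14 = 11% of the target difference.
- Middle: 0.30 × 0.20 = 6 points; 6 / 14 = 43%.
- Largest: 0.30 × 0.30 = 9 points; 9 / 14 = 64%.

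**5. Resulting false-positive rate.** With mean comprehension 60% and 216 per group, the standard error is √(2 × 0.6 × 0.4 / 216) = 0.047 for independent visits. For clustering, 648 / 46 = 14.1 surveys per provider (46 = 55 − 9 assumed lost). The design effect is 1 + 13.1 × ICC, which is 1.65 at ICC 0.05 and 2.31 at ICC 0.10. The ICCs are assumed, and the sketch treats each provider as belonging to one group.

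Rejection rate = Φ(d/SE − 1.96) + Φ(−d/SE − 1.96).

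| Spurious difference | Independent | ICC 0.05 | ICC 0.10 |
|---|---|---|---|
| 1.5 points | 6% | 6% | 5–6% |
| 3 points | 10% | 8% | 7% |
| 6 points | 25% | 17% | 13% |
| 9 points | 48% | 32% | 24% |

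Clustering lowers these rates because the honest standard error is larger; the bias in the estimate is unchanged. The rates come from a simple unadjusted test, not from the planned adjusted weighted GEE.

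**The case against.** The article claims only that randomisation will help, not that it prevents confounding. The plan also has more than imputation: covariates, a restricted survey population, summaries by strategy, and steps to raise response (audio, several modes, a 7-day window, incentives). An article need not print recruitment rules, and the full protocol may contain them. All of this stands. It bears on how large the bias might be, and it makes the absence of a sampling rule no finding. It does not make the inference in Data analysis valid for H2.

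Three stronger readings are tempting and are not supported.
- A reader might infer that the staff who randomise also recruit and survey. The sequence is generated and handled "using a sequence generated by the study biostatistician and implemented by a research coordinator", and some surveys are completed "over the telephone with a bilingual research coordinator or professional interpreter". These are two separate statements sharing a job title. The article does not say who approaches patients, or that those people know the allocation.
- A reader might divide 648 by the 5796 planned encounters (11%) to show wide room for selection. The 5796 cover all languages and visit types, while survey eligibility is acute visits in four languages, and that denominator is not given. A low sampling fraction also causes no bias by itself.
- A reader might take the 48% above as the expected error rate. It is the extreme corner of assumed inputs, for independent visits and an unadjusted test.

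**Conclusion.** The point holds as a flaw in stated reasoning, with a gap in the analysis that follows from it. For H2, randomising providers does not protect against differences by strategy in who is surveyed, and the planned imputation does not address unsurveyed eligible visits. The existing covariates, restrictions and summaries may reduce or reveal part of the problem, so it would be wrong to say that nothing planned bears on it.

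Whether bias will occur, its direction and its size cannot be derived from the document; the 1.5 to 9 points rest wholly on the assumed gaps and mix differences. The comprehension outcome, and through it H4b, is affected. The primary interpreter-use outcome is not affected in this way. The repair is a cheap improvement rather than a condition for the trial's validity.

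**What to change.** 1. **Data analysis:** limit the statement that randomisation protects against unobserved confounding to interpreter use. Say that for comprehension, selection into the survey after allocation is a separate concern.
2. **Aim 1, H2 – comparison:** using the administrative data already held, compare surveyed visits with all eligible visits (acute, four languages) of enrolled providers, by strategy and phase.
3. **Aim 1, H2 – sensitivity analysis:** weight surveyed visits by the inverse of their probability of being surveyed. Estimate this at visit level, within strategy and phase, from age, sex, race/ethnicity, insurance, language and whether the visit was interpreted. State that this handles measured selection only; health literacy, education and English proficiency come from the survey alone and cannot enter these weights.

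The cost is one extra analysis on existing data and a somewhat wider interval for it. A randomly drawn list of visits to approach, with a log of patients approached, declined or missed, would help further. It is optional here, because the full protocol may already set recruitment rules and such a list could make recruitment less flexible.
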